## Abstract

**Background:**

Frailty is a highly prevalent condition in old age leading to vulnerability and greater risk of adverse health outcomes and disability. Detecting and tackling frailty at an early stage can prevent disability. The purpose of this study is to evaluate the effectiveness of a multifactorial intervention program to modify frailty parameters, muscle strength, and physical and cognitive performance in people aged 65 years or more. It also assesses changes from baseline in falls, hospitalizations, nutritional risk, disability, institutionalization, and home-care.

**Methods/design:**

The current study is a randomised single-blind, parallel-group clinical trial, with a one and a half year follow-up, conducted in eight Primary Health Care Centres located in the city of Barcelona. Inclusion criteria are to be aged 65 years or older with positive frailty screening, timed get-up-and-go test between 10 to 30 seconds, and Cognition Mini-Exam (MEC-35) of Lobo greater than or equal to 18. A total of 352 patients have been equally divided into two groups: intervention and control. Sample size calculated to detect a 0.5 unit difference in the Short Physical Performance Battery (Common SD: 1.42, 20% lost to follow-up). In the intervention group three different actions on frailty dimensions: rehabilitative therapy plus intake of hyperproteic nutritional shakes, memory workshop, and medication review are applied to sets of 16 patients. Participants in both intervention and control groups receive recommendations on nutrition, healthy lifestyles, and home risks.

Evaluations are blinded and conducted at 0, 3, and 18 months. Intention to treat analyses will be performed. Multivariate analysis will be carried out to assess time changes of dependent variables.

**Discussion:**

It is expected that this study will provide evidence of the effectiveness of a multidisciplinary intervention on delaying the progression from frailty to disability in the elderly. It will help improve the individual’s quality of life and also reduce the rates of falls, hospital admissions, and institutionalizations, thus making the health care system more efficient. This preventive intervention can be adapted to diverse settings and be routinely included in Primary Care Centres as a Preventive Health Programme.

**Trial registration:**

ClinicalTrials.gov PRS:NCT01969526. Date of registration: 10/21/2013.

## Background

The concept of frailty has long been associated with advancing age although only recently has it been specifically defined as a medical syndrome[1–4]. Disability, comorbidity, malnutrition, biological changes, cognitive impairment, dependency needs, and demands for social services are directly age-related; age, however, as an isolated criterion is not enough to identify vulnerability[5].

Despite considerable discussion, frailty remains to be systematically defined[6]. There is evidence that it increases proportionally to an accumulation of deficits[7]; acute problems -falls, fractures, and infections-, progressive loss of autonomy, and psychosocial limitations all lead to disability and a higher risk of hospitalization, institutionalization, and death[8, 9].

There is no agreement on a valid evaluation model for both research and clinical approaches[10], and some authors differentiate between physical and cognitive frailty[11]. The standard clinical proposal is that which has been presented by Fried *et al*. who identify someone as having a frail phenotype when three or more of the following components are presented[3]: unintentional weight loss (4.5 kg (=10 lbs) in the past year), self-reported exhaustion (two positive questions of Center for Epidemiologic Studies Depression Scale (CES-D)), weakness, slow walking speed, and low levels of physical activity. Such a definition would be mainly related to physical frailty. For rapid frailty screening of a community-living elderly population these five criteria, however, do not represent a pragmatic approach[10]. Avila-Funes *et al*. proposed a review to slightly modify Fried’s measurements in order to strengthen the predictive validity of the concept[12], with variable results[13, 14]. In addition, Gill *et al*. introduced two tests of physical ability strongly associated with disability development and progression: the Rapid-Gait Test and the Stand-Up Test[15]. Other useful batteries of physical performance, such as the Short Physical Performance Battery (SPPB) from Guralnik, can also be found as predictors of old age disability[16, 17].

Sarcopenia is linked to physical frailty and is a key feature of this condition in older people[18]. In fact, a non-negligible proportion of elderly individuals are moderately affected by this it[19]. Sarcopenia is related to loss of muscle mass and muscle strength, strong predictors of adverse health outcomes[20] and death[21, 22].

Epidemiological studies have linked physical frailty and cognitive impairment: frailty increases the risk of cognitive decline and cognitive impairment increases the risk of frailty, therefore, both dimensions would benefit from being addressed[23, 24].

Identifying interventions to prevent or delay the loss of autonomy is currently a public health priority for the successful management of the ageing[25, 26]. Multidimensional home interventions have revealed some benefits, although conclusions are inconsistent and seem to be dependent on factors such as the provider’s experience, access to monitoring, and duration of the follow-up program[15].

A comprehensive geriatric assessment, followed by a multidimensional intervention on disability risk factors -medical, functional, psychological, and environmental problems- through disease management and health promotion in a low-risk elderly population, succeeds in reducing institutionalization and the risk of falls, delaying disabled functional decline, and improving physical performance. The effects, however, are not statistically significant[27–29].

Strategies involving mass screening in Primary Care to apply preventive approaches based on healthy ageing advice, long-term exercise programs, assistance devices including home telecare kits[30], and environmental modifications can reduce falls[31]. Nevertheless, when considered separately, these methods have no impact on reducing disability[32].

Exercise programs improve strength, aerobic capacity, balance, and function[33, 34], but these benefits depend on long-term adherence, extended training, and exercise-related behaviours acquired in early life. The most promising strategies to increase physical activity in the elderly are those which provide appropriate written advice and generate feelings of fun and satisfaction[35].

Recent surveys have put forward new strategies for the management of sarcopenia to slow down the decline of muscle features: resistance training in combination with adequate protein and energy intake and, additionally, treatment of vitamin D deficiency[36, 37].

Nutritional interventions alone show weak correlation with health improvement in the vulnerable, elderly population. However, dietary advice in association with protein supplementation intake seems to have some effects on sarcopenia, inducing muscle hypertrophy, accelerating weight gain in undernourished older people[38], and reducing fractures[39]. There is a lack of evidence, however, concerning its effects on mortality and hospital admission rates[40].

Findings from cognitive training studies show positive effects. Memory training can aid maintaining long-term improvement in performance[41, 42].

Exercise also leads to enhanced cognitive functioning and psychological well-being in frail, older adults[43]. Aerobic exercise has shown effects on some measures of cognitive function, without consistency for all values[44].

There are few randomized, controlled trials concluding that cognitive interventions, plus complementary physical exercise, can produce significant global improvements in cognitive function, and quality of life, and delay the onset of disability[45].

What about medication use in frail, older adults? The rates of adverse drug events are higher in the elderly population, as many of them have comorbidities, multiple drug prescriptions, and deteriorated physical and cognitive impairment[46]. In the previous decade, deprescribing, based on clinical and ethical criteria, has been defended as an option for managing chronic conditions, avoiding adverse effects, and improving patient outcomes. Polypharmacy has been independently associated with an increase of mortality in the elderly[47], indeed, several multifaceted interventional studies have demonstrated that medication review has a positive effect on reducing mortality, hospital admissions and falls, and enhances quality of life[48].

Such a wide range of interrelated factors gives weight to our proposal to conduct a multifactorial intervention aimed at non-disabled, i.e. frail, elderly individuals. Our objective is to focus on this population whose health status still permits some positive modifications in the inevitable evolution from frailty to dependence so that by preventing home confinement or institutionalization, older people can stay active and live by themselves in the community.

### Study aim

This is a research protocol for a randomized, controlled trial aimed at assessing the effectiveness of a multifactorial intervention program to modify parameters of frailty, muscle strength, and physical and cognitive performance in elderly people living in the community. The intervention includes various professional disciplines and is based on physical activity, diet supplementation, memory workshops, and medication review.

Secondary aims include evaluating changes in rates of falls fractures, hospital admissions, inclusions in home care programs, and institutionalizations.

## Methods/design

### Study design

The study design is a single-blind, parallel-group, pragmatic, randomised, clinical trial with one year and a half follow-up.

Changes from baseline measurements (month 0) in the parameters of frailty, muscle strength, and physical and cognitive performance are compared between the intervention (IG) and control group (CG) at the end of the intervention (month 3). An 18 month follow-up after randomization will be established in order to determine whether intervention effects can be sustained. The 18 month changes in rates of falls, fractures, hospital admissions, inclusions in home care programs, institutionalizations and vital status will be analysed.

The CONSORT Statement extensions for trials of non-pharmacological interventions and pragmatic intervention trials were used to design the study and will be used to report it.

### Sample size calculation

Sample size has been calculated to detect minimal significant effects on the variable of physical performance (SPPB): Accepting an alpha risk of 0.05 and a beta risk of 0.20 in a bilateral contrast, 318 individuals are required in order to detect a difference equal to or greater than 0.5 units in the SPPB[49, 50]. The common standard deviation has been taken to be 1.42. A drop-out rate of 20% is anticipated. Finally, 352 subjects have been included (n = 176 IG and n = 176 CG).

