#### Intervention

The intervention consists of a triple disability preventive therapy, consecutively applied to each subject in the intervention group, in groups of 16 participants (see Table 3):

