Rehabilitation therapy plus the posterior intake of 1 hyperproteic nutritional shake which is then taken daily for 1 month. All patients in the intervention group perform the aerobics exercise plan in the primary care centre, 60-minute session twice a week on non-consecutive days for 6 weeks (12 sessions of 60 minutes each). Subjects must incorporate a progressive increase in the intensity of the exercise in each session. One session a week is dedicated to work with balance and the other to strength training. Both balance and strength are based on functional exercises. All sessions begin with a warm up for 5 minutes, and end by cooling off for another 5 minutes with relaxing exercises. The sessions are conducted under the supervision of a specialist in physical activity. A hyperproteic nutritional shake is provided at the end of each session, and the amount of shakes needed for one month’s consumption post-physical therapy is assigned. The safety of the exercise program is measured by reviewing the record sheet for each patient in the training program, ascertaining cardiovascular decompensation and musculoskeletal injuries.Memory workshops. Two speech therapists from the rehabilitation unit conduct 12 sessions of practical exercises (written, oral, corporal, and musical) in groups of 16 participants. Each of the 12 sessions lasts 90 minutes and is conducted twice a week. Each person in the intervention group has their own material to work short and long-term memory, with exercises for the identification of figures and images, evocation of words, true or false sentences, crosswords, completion of unfinished sentences, and other language exercises such as synonyms and antonyms.Medication Review. Reduction of potentially inappropriate medications, especially in polymedicated patients, after review from general practitioners. A patient is considered to be polymedicated when taking more than five medications daily and continuously for a period not less than six months. Medication review follows the Screening Tool of Older Persons’ potentially inappropriate Prescriptions (STOPP) criteria [60]. In addition to the review of medication, verbal guidance on each of the drugs consumed is also provided. After an e-mail sent with the changes suggested by two doctors from the Project Group, this intervention is carried out by every patient’s general practitioner, during the first month of the intervention, in a maximum of 3 clinical interviews for that purpose. It especially focuses on reducing the consumption of benzodiazepines or other psychotropic drugs.

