### Statistics

Intention to treat analyses will be performed. Baseline characteristics will be compared between groups by independent t tests and Chi-square tests. Outcome variables will be calculated for each individual and time point (difference between the result of SPPB, muscle strength, and other frailty variables in each time point and the initial value), and 95% confidence intervals for the differences between groups will be calculated. Data will be analysed using repeated measures analysis of variance (ANOVA) consisting of intervention and control groups and time (baseline, post-intervention, follow-up).

Also, for longitudinal adverse outcome measures (disability, home care inclusion, institutionalization or death), survival analyses using Cox’s regression models will be applied. The statistical significance level will be set at p <0.05.

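### Intervention delivered in groups of 16, but sample size and named analysis treat all participants as independent: type I error exceeds 5% if outcomes within a set are correlated

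*Protocol article*

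**What the plan says.** All places are in the protocol article.

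- **Randomisation** (text below Figure 1): simple randomisation of individuals.
- **Delivery** (Intervention): the programme is "consecutively applied to each subject in the intervention group, in groups of 16 participants". For the memory workshops, two speech therapists "conduct 12 sessions of practical exercises (written, oral, corporal, and musical) in groups of 16 participants". The exercise plan has 12 supervised sessions of 60 minutes at the primary care centre. The medication review is done by each patient's own general practitioner.
- **Control group**: usual care, plus an invitation to two group advice sessions of unstated size.
- **Sample size calculation**: "Accepting an alpha risk of 0.05 and a beta risk of 0.20 in a bilateral contrast, 318 individuals are required". The target effect is an SPPB difference of 0.5, with an SD of 1.42 in both arms and a loss of 20% allowed for. On the number actually enrolled, the paragraph ends: "352 subjects have been included (n = 176 IG and n = 176 CG"). No ICC, design effect or set size appears there.
- **Statistics**: "Data will be analysed using repeated measures analysis of variance (ANOVA) consisting of intervention and control groups and time". No set, therapist or centre term is named.

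**The concern.** Allocation is individual, but once allocated, intervention participants share 12 exercise sessions of 60 minutes and 12 memory workshops of 90 minutes, about 30 hours, with the same peers and at the same pace. Controls share little of this. That is a partially nested design: a source of correlation exists in one arm and is largely absent in the other. SPPB and the memory tests are the outcomes these sessions target, so they are the ones most exposed.

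An analysis that ignores the sets counts 16 correlated participants as 16 independent ones. For any positive set-level ICC, the standard error of the arm difference is understated, confidence intervals are too narrow and the false-positive rate exceeds the nominal 5%. A test that does allow for the sets has less power than the independent-data calculation promises. The article wants the programme considered for wider implementation if it proves effective, so overstated evidence would matter.

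**Working it through.** **Inputs from the article:** two-sided alpha 0.05, power 0.80, difference 0.5, SD 1.42, dropout 20%, 352 included (176 per arm), groups of 16.

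**Assumptions:** 176/16 = 11 equal sets; loss spread evenly, so 16 × 0.8 = 12.8 retained per set; total variance 1.42² in both arms; clustering in the intervention arm only; one arm comparison with that SD. The ICC is not in the article and is varied from 0 to 0.10.

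**1. The article's own figure.** n per arm = 2 × (1.96 + 0.8416)² × 1.42² / 0.5² = 126.6, rounded up to 127. Evaluable total 254; 254/0.8 = 317.5, rounded up to 318. This reproduces exactly and leaves no room for a design effect.

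**2. The 352 included, under independence.** 176 × 0.8 = 140.8 per arm. SE₀ = 1.42 × √(2/140.8) = 0.169. Power = Φ(0.5/0.169 − 1.96) = 84.0%.

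**3. With sets in the intervention arm.**
- Design effect in that arm: DE = 1 + (12.8 − 1) × ICC
- True standard error: SE = 1.42 × √(DE/140.8 + 1/140.8)
- Type I error of the unadjusted test: 2 × [1 − Φ(1.96 × SE₀/SE)]
- Power of a valid clustered test (normal approximation): Φ(0.5/SE − 1.96)
- Satterthwaite version: non-central t, with 10 degrees of freedom for the 11 sets combined with 139.8 for controls

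Example at ICC 0.05: DE = 1.59; SE = 1.42 × √(2.59/140.8) = 0.193; SE/SE₀ = 1.14; type I error 8.5%; power 73.8%.

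| ICC | DE | Type I error, unadjusted test | Valid test, 352, normal | Valid test, 352, Satterthwaite | Valid test, 318, normal |
|---|---|---|---|---|---|
| 0 | 1.00 | 5.0% | 84.0% | 82.1% | 80.1% |
| 0.01 | 1.12 | 5.7% | 81.9% | 79.6% | 77.8% |
| 0.02 | 1.24 | 6.4% | 79.8% | 77.3% | 75.6% |
| 0.05 | 1.59 | 8.5% | 73.8% | 70.5% | 69.3% |
| 0.10 | 2.18 | 12.0% | 64.9% | 60.8% | 60.5% |

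The Satterthwaite value at ICC 0 is the price of keeping the set term when it is not needed. The 318 column uses 127 per arm with 12.8 per set and should be compared with the normal column for 352.

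**4. Margin from the extra participants.** Setting power to 80% for 352 (normal approximation) gives an ICC of about 0.019, or about 0.015 if 16 rather than 12.8 per set is used in the design effect.

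**5. The planned test's own rejection rate at a true difference of 0.5.** Φ((0.5 − 1.96 × SE₀)/SE) gives 84.0 / 83.3 / 82.7 / 80.9 / 78.5% at ICC 0 / 0.01 / 0.02 / 0.05 / 0.10.

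**The case against.** A reader might infer that the trial's 80% power is lost and its p-values are invalid. The article does not support that as a flat statement. Both depend on an ICC that it does not give. The 80% is attached to 318, and the 352 included start from 84% under independence.

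The inflated type I error and the lost power also belong to different tests. Step 5 shows the unadjusted test still rejecting about 80% of the time up to ICC 0.05, but at an inflated alpha. The charge against the planned test is therefore its type I error; the power loss appears once a valid test is used.

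Several supposed sources of correlation are weaker than they look:
- The article never says that set membership is fixed, and the 11 sets are inferred.
- Shared centre does not set the arms apart, since individuals from all 8 centres are randomised.
- If the same two speech therapists run every workshop, they add no variance between sets.
- The medication review is not a set session.
- Controls are offered two group sessions, so their independence is approximate.

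These points favour the lower part of the ICC range. They do not make the ICC zero, because shared peers and pace over about 30 hours remain.

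Finally, a journal article may leave random-effect structure to a fuller document, and the abstract speaks of multivariate analysis. That is fair as to detail. But this article does name the model and its factors, and that model does not match the delivery it describes.

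**Conclusion.** The point holds in conditional form and should be fixed. The sample size and the named ANOVA assume independence, while the main contact components are delivered in groups of 16 in one arm only. For any positive set-level ICC the planned arm comparison exceeds 5% type I error: modestly at ICC 0.01 to 0.02 (5.7 to 6.4%), materially at 0.05 to 0.10 (8.5 to 12.0%).

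For power, the 34 extra participants absorb an ICC up to about 0.019 by the normal approximation. With Satterthwaite degrees of freedom, power is already just below 80% at ICC 0.01. The extra participants do nothing for type I error, which is the main reason to act.

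The sizes rest on the assumed ICC range, equal sets, even loss, and clustering confined to the intervention arm.

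**What to change.** 1. Record the set number for each intervention participant.
2. Analyse SPPB and the other continuous outcomes with a linear mixed model containing arm, time and their interaction; a centre term for both arms; a random set effect in the intervention arm only; and Satterthwaite or Kenward-Roger degrees of freedom. The centre term keeps centre differences, which controls share, from being attributed to sets.
3. Keep 318 as the independent-data figure, and state power for the 352 included as conditional on an assumed ICC range of 0 to 0.10.

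**Cost:** one identifier, revised wording under Statistics and Sample size calculation, somewhat wider confidence intervals (standard error up by a factor of 1.14 at ICC 0.05) and a less favourable stated power. If the ICC is near zero, the loss is small: 82% instead of 84%. No extra patients are needed.

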### Ethical aspects

Written informed consent has been obtained from all recruited subjects. Objectives, tests and other details about methodology and interventions were explained orally and in writing. The trial was approved by the Ethics Committee of the IDIAP Jordi Gol (code number P12/047) on June 1st, 2012. Funding from the Carlos III Health Institute was granted on December 20, 2012 (project code PI12/01503).

### Participants and recruitment

From February 2013 to January 2014, 370 individuals aged 65 years and over were recruited from 8 Primary Healthcare Centres (PHCC) located in two different districts of Barcelona. A total population of 33,857 aged 65 years and over live in the reference area.

Subjects were recruited by referral from the PHCC where the opportunity to participate in the study was offered on a regular daily basis to all patients meeting preliminary frailty criteria (Barber Questionnaire[51]). Eligibility was then verified with an assessment by a Case Management Nurse (CMN) through a personal interview. Participants meeting at least 3 Fried modified frailty criteria were included whilst those individuals with very slow or rapid gait speed, or cognitive impairment based on MEC-35 of Lobo[52], were excluded.

Inclusion and exclusion criteria are shown in Table 1.

The flow-chart of the trial according to CONSORT 2010 is visualized in Figure 1.

